### Interim analyses {21b}

Not applicable, no interim analyses for safety, efficacy or futility will be performed. Safety within the trial will be monitored by an installed Data Safety Monitoring Board (DSMB).

### Methods for additional analyses (e.g. subgroup analyses) {20b}

Not applicable.

### Methods in analysis to handle protocol non-adherence and any statistical methods to handle missing data {20c}

We follow the guideline in handling missing data [31]. When it concerns missing completely at random (MCAR) or missing at random (MAR), multiple imputation will be used. Imputing then will always increase the precision and often also reduces bias. However, when data are missing not at random (MNAR), best-worse and worse-best sensitivity analyses will be added. For missings in the continued T2T group, this would mean replacing missing values for continued remission in the best-case scenario and no remission values in the worst-case scenario.

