### Sample size {14}

The null hypothesis is that no statistical difference is found between the continued T2T approach and the T2S discontinuation approach. Since the T2S group receives less intensive treatment, the superiority of the T2S discontinuation approach in terms of efficacy is considered unlikely and also irrelevant. After all, one would prefer the less intensive treatment as long as the more intensive treatment is not clearly superior, regardless of whether the less intensive treatment is equally effective or superior. Therefore, we use a one-sided test to achieve the same power to show the superiority of continued T2T with a smaller study size compared to a two-sided test with the same alpha.

Based on earlier studies and on unpublished data from our own cohort (2400 gout patients from Sint Maartenskliniek, Radboudumc and Rijnstate) we estimate that 8% of gout patients following the treat-to-target strategy experience at least 1 gout flare during the 2-year follow-up and 4% of patients are not in remission in the last 6 months of the 24-month follow-up. For the patients in the treat-to-symptom group, less data is available, but we estimate that 12% are not in remission in the last 6 months of the follow-up time, based on the 5 smaller cohort studies included in the review of Beslon et al [11].

Using alpha 0.05, power 1-beta 0.80, one-sided superiority testing with a two proportion *z* test, and expected proportion of patients not fulfilling the adapted preliminary remission criteria for gout domains during the last 6 months of the study of 0.04 and 0.12 in the T2T strategy and control group T2S strategy (difference 0.08, number needed to harm, number needed to harm, NNH, 12), 278 analysable patients are needed. Accounting for 10% dropout, 310 patients will be included. If during follow-up dropout turns out to be lower (based on incidence density of dropout/patient-years), fewer patients will be included.

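### The check for informative missingness is triggered only if data are MNAR, which the data cannot show, and its only named method is an all-or-nothing bound that is very wide at the planned dropout

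*Protocol article*

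**What the plan says.** Section {20c} of the protocol article sorts the handling of missing data by mechanism. For the first two mechanisms: "When it concerns missing completely at random (MCAR) or missing at random (MAR), multiple imputation will be used". For the third: "when data are missing not at random (MNAR), best-worse and worse-best sensitivity analyses will be added". The extreme scenarios are illustrated for the continued T2T arm as "replacing missing values for continued remission in the best-case scenario and no remission values in the worst-case scenario". The section gives no criterion for deciding which mechanism applies and names no scenario between the two extremes.

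The Sample size section {14} sets the scale: non-remission proportions "of 0.04 and 0.12 in the T2T strategy and control group T2S strategy (difference 0.08"), "278 analysable patients are needed", and "Accounting for 10% dropout, 310 patients will be included". The same section allows fewer inclusions if dropout proves lower. Section {17a} states that patients, nurses and physicians are not blinded. Section {18b} says that data collected before loss to follow-up or withdrawal of consent will be used.

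**The concern.** Whether missingness is MAR or MNAR depends on the values that were not seen. A sensitivity analysis conditional on MNAR therefore rests on a judgement that cannot be tested and that may be made after the data are known. An analyst who asserts MAR has complied with the plan and has examined no departure from it.

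This matters more here than in a blinded trial. Section {17a} and the Discussion both expect that patients who stop ULT may anticipate more flares. Withdrawal related to symptoms, and differing by arm, is plausible, although the documents give no figure for it.

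If the check is triggered, the second problem is its form. The bounds move the difference by the full missing fraction in each direction. With an 8-point target effect and 10% dropout planned, that width may leave the check unable to distinguish a robust result from a fragile one.

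**Working it through.** **Inputs.** From Sample size {14}: 4% (T2T) and 12% (T2S) not in remission, one-sided alpha 0.05, power 0.80, two-proportion z test, 278 analysable, 310 included, 10% dropout. From Sequence generation {16a}: 1:1 allocation, so 155 per arm. Assumptions added here: 10% of primary outcomes missing in each arm, every dropout lacking the outcome, and observed rates equal to the planned ones.

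**Reproducing the plan's figure.** With unpooled variance, n per arm = (1.645 + 0.842)² × (0.04×0.96 + 0.12×0.88) / 0.08² = 139.1. Two arms give 278.2, against 278 stated. 278 / 0.90 = 308.9, so 309, or 310 as an even total. Both figures reproduce.

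**Bounds at 10% missing.** Missing per arm: 15.5. Observed per arm: 139.5. Observed non-remissions: 0.04 × 139.5 = 5.58 (T2T) and 0.12 × 139.5 = 16.74 (T2S). Differences are T2S minus T2T, with the pooled z test and one-sided p.

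- Observed cases only: +8.0 points, z = 2.46, p = 0.007.
- T2T best, T2S worst: 5.58/155 = 3.6% and (16.74 + 15.5)/155 = 20.8%; +17.2 points, z = 4.63, p < 0.00001.
- T2T worst, T2S best: (5.58 + 15.5)/155 = 13.6% and 16.74/155 = 10.8%; -2.8 points, z = -0.75, p = 0.77.

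In general, with missing fraction d per arm, the bounds are (1 - d) × 8 points ± 100d points. At d = 0.10 this is 7.2 ± 10. The span of 20 points is 2.5 times the planned effect.

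**Unfavourable bound by missing fraction, planned effect held at 4% versus 12%.**

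| Missing per arm | Difference (points) | One-sided p |
|---|---|---|
| 1% | +6.9 | 0.014 |
| 2% | +5.8 | 0.035 |
| 3% | +4.8 | 0.074 |
| 5% | +2.6 | 0.22 |
| 7.5% | -0.1 | 0.51 |
| 10% | -2.8 | 0.77 |

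**The same bound with a larger effect, 10% missing.** If observed T2S non-remission were 23%, the bound is 13.6% versus 20.7%, p = 0.049. At 30% it is 13.6% versus 27.0%, p = 0.002.

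**A graded analysis of the planned scenario.** Take 139 observed and 16 missing per arm, and let missing T2S patients be in non-remission at 12%, so T2S is 12.0% overall. Vary k, the number of missing T2T patients not in remission; the T2T rate is (0.04×139 + k)/155.

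- k = 4 (25% of the missing): 6.2% versus 12.0%, +5.8 points, p = 0.037.
- k = 5 (31%): 6.8% versus 12.0%, +5.2 points, p = 0.059.

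The conclusion tips when about a quarter to a third of missing T2T patients have lost remission, against 4% of those observed. A clinical reader can judge whether that is believable. A range of -2.8 to +17.2 gives no such threshold.

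**The case against.** The strongest reply is that best/worst case is a recognised bounding method, that section {20c} adds it to multiple imputation rather than substituting it, and that this is a condensed article. It cites a missing-data guideline and an available full protocol, neither of which is at hand. Tipping-point details and the content of an imputation model are commonly left to the analysis plan, so their absence is not itself an error. That stands. It does not reach the trigger, which the article states and which cannot be applied as written.

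The assumed 10% missing is at the upper end. Under Table 3 all criteria must be met, so a patient with a recorded flare or a raised score in the last six months, or a visible tophus at any time in follow-up, is already an observed non-remission even if later lost. Section {14} also expects that dropout may be lower. This too stands, and the table above shows the effect of smaller fractions.

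A reader might infer more than the documents support:

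- That the bounds overwhelm any effect and make every result look fragile. They do not: the unfavourable bound holds at 2% missing with the planned effect, and at 10% missing once observed T2S non-remission reaches about 23%.
- That restarting ULT drives patients out. Sections {6b} and {11b} make restart part of the T2S strategy, so it gives no reason to leave the trial.
- That imputation will rest on arm and baseline alone, so that "Imputing then will always increase the precision and often also reduces bias" is a substantive error. The section sets no such limit, and monthly flare and three-monthly questionnaires are collected. The word always is too strong, but changing it alters no analysis.

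**Conclusion.** The concern holds in two linked parts. First, the sensitivity analysis depends on a condition that observed data cannot establish, so the plan permits a primary result with no check of MAR. This rests on the text alone and on no numerical assumption. Second, the only MNAR method named is all-or-nothing. If 10% of outcomes were missing in each arm and observed rates matched the planned ones, it would give -2.8 to +17.2 points: one scenario strongly favouring T2T, the other reversed in sign. At the planned effect it supports superiority only up to about 2% missing per arm. Lower missingness or a larger true effect would make the bounds more useful.

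The documents do not show that dropout will be informative, only that the design makes it plausible. The primary test and the sample size are unaffected.

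**What to change.** In the analysis plan, replace the conditional sentence with a commitment to run the sensitivity analysis whenever any primary outcome is missing. Keep multiple imputation as the main approach, and state that the imputation model uses the interim flare, NRS and ULT-restart data already collected. Add a delta-adjusted tipping-point analysis that varies the non-remission odds of missing patients separately by arm and reports where the conclusion changes. Retain best/worst case as outer bounds only. As a minor wording point, say that imputation can increase precision, not that it always does.

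The cost is a few sentences and a few extra runs. Data collection, trial conduct and sample size do not change.

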### Plans to give access to the full protocol, participant-level data and statistical code {31c}

The full protocol is available at https://zorgevaluatienederland.nl/evaluations/go-test-finale. The data collected during the study will be available at reasonable request.

### Adverse event reporting and harms {22}

Adverse events (AE) are defined as any undesirable experience occurring to a subject during the study, whether or not considered related to the trial procedure. All AEs reported spontaneously by the subject or observed by the research physician, or his staff will be recorded. A serious adverse event (SAE) is any untoward medical occurrence or effect that; results in death; is life-threatening (at the time of the event); requires hospitalization or prolongation of existing inpatients’ hospitalization; results in persistent or significant disability or incapacity or any other important medical event that did not result in any of the outcomes listed above due to medical or surgical intervention but could have been based upon appropriate judgement by the investigator. Elective hospital admissions will not be considered as a SAE.

The research physician of the Sint Maartenskliniek will report the SAEs through the web portal to the accredited METC Oost-Nederland within 7 days of first knowledge for SAEs that result in death or are life-threatening followed by a period of a maximum of 8 days to complete the initial preliminary report. All other SAEs will be reported within a period of a maximum of 15 days after the sponsor has first knowledge of the serious adverse events. All AEs will be followed until they have abated, or until a stable situation has been reached. Depending on the event, follow-up may require additional tests or medical procedures as indicated, and/or referral to the general physician or a medical specialist.

In addition, a safety report is sent to the accredited METC Oost-Nederland once a year.

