#### Secondary objectives

To exploratory assess non-inferiority (only when superiority cannot be demonstrated) of the treat-to-symptom strategy compared to the treat-to-target strategy.To assess the between-group difference in the incidence (cumulative incidence and incidence density) of gout flares during the follow-up period of 24 months according to gout flare criteria [23].To assess the proportion of participants that require reintroduction of ULT in the T2S discontinuation strategy group.To assess the between-group difference in the use of ULT and gout flare medication (anti-inflammatory medication).To assess predictors for successful ULT cessation in the T2S discontinuation strategy group including clinical, radiological, immunological, and genetic variables.To evaluate the between-group difference in Patient-Reported Outcome Measures, by three monthly analysing the 5-level EuroQol-5 domains (EQ-5D-5L) questionnaire, functioning by using the Health Assessment Questionnaire Disability Index (HAQ-DI), numeric rating scale (NRS) for pain and NRS global health.To assess the between-group difference in types and frequency of adverse events, with a special focus on change in the renal function defined by Glomerular Filtration Rate Chronic Kidney Disease – Epidemiology Collaboration (GFR-CKD-EPI) and incidence of major adverse cardiovascular events (defined as arrhythmia, non-fatal stroke, non-fatal myocardial infarction, (hospitalization for) acute coronary syndrome, cardiovascular hospitalizations and cardiovascular death) during the follow-up period of 24 months. For the MACE there is a special interest in the first 3 to 6 months after ULT cessation and reintroduction of ULT in the T2S group.To assess the (between-group) difference in prescribed medication compared with refill rates during the follow-up period of 24 months.To assess the incremental cost-effectiveness of a T2T ULT continuation strategy compared to a T2S ULT discontinuation strategy.

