## Interventions

### Explanation for the choice of comparators {6b}

Since we hypothesize that a T2T ULT continuation strategy is superior compared to a T2S ULT discontinuation approach in gout patients in remission, the control group is the T2S discontinuation strategy group.

In the T2S strategy, ULT is tapered to stop and restarted in case of recurrent or persistent flaring or the emergence of tophi. Thereafter, (re)treatment is T2T, thus also based on serum urate levels. ULT is tapered to stop in a maximum of 6 weeks based on ULT dosage at baseline (Table 2). A taper strategy was recommended over a direct stop strategy by the regional medical review board. This was based on studies that showed associations between cardiovascular events and the start/stop of ULT, presumably due to rapid serum urate changes. Tapering is expected to prevent rapid serum urate changes and thereby serious cardiovascular adverse events. Two weeks after ULT cessation an extra blood sample is obtained to check for any changes in blood counts and kidney and liver function. Serum urate levels will most likely increase, but this is not acted upon as in the T2S discontinuation strategy, ULT treatment is based only on symptoms. A telephone consult is planned three weeks after ULT cessation to verify that ULT has indeed been stopped, to discuss the tapering process and to discuss the blood results.

**Table 2 Tab2:** Tapering schedules of urate-lowering therapies in the treat-to-avoid-symptoms discontinuation group

**Baseline dose**	**First tapering step at baseline**	**Second tapering step 2 weeks from baseline**	**Third tapering step 4 weeks from baseline**	**Fourth tapering step 6 weeks from baseline**

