### Participant timeline {13}

During follow-up, three hospital visits are scheduled at the outpatient clinic, at baseline, month 12 and month 24 for both treatment strategy groups. For patients randomized to the T2S discontinuation group, 2 weeks after complete ULT cessation an extra blood sample is obtained and a telephone consult is scheduled one week later to discuss results and make sure patients indeed stopped the ULT (Fig. 2). Questionnaires are sent monthly (gout flare questionnaire) and three monthly (other questionnaires).

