During the study, adverse events are registered using the Common Toxicity Criteria for Adverse Events. The results will be presented by using descriptive statistics. The occurrence of adverse events between the groups is compared using a chi-squared test or Fisher’s exact test.To assess the between-group difference in use of ULT and flare medication (colchicine, NSAIDS and/or glucocorticoids).

Per group, the proportion of patients using flare medication, restarting ULT or experiencing a ULT increase/decrease will be described as *n* (%). The difference between the groups will be analysed using a chi-squared test or Fisher’s exact test.To assess the between-group difference in prescribed medication compared with refill rates and self-reported adherence during the follow-up period of 24 months.

First, it will be examined per group whether the self-reported medication use corresponds with the refill adherence information from the pharmacy/LSP, this is described by means of *n* (%). Then the difference between the two treatment groups will be compared by using a chi-squared test or Fisher’s exact test.To assess predictors for successful ULT cessation in de T2S strategy group including clinical, radiological, and immunological, variables.

Regression analyses will be used to exploratory identify possible predictive variables for unsuccessful withdrawal of uric acid-lowering medication. This will include radiological, biochemical, patient and disease characteristics.

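### The adverse event comparison is biased towards more recorded events in T2S, because only T2S has a scheduled safety blood sample and call between baseline and month 12

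*Protocol article*

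**What the plan says.** Between-arm safety is a declared secondary objective: "To assess the between-group difference in types and frequency of adverse events, with a special focus on change in the renal function" and on major cardiovascular events (Secondary objectives). The analysis is given under Statistical methods {20a}, Secondary outcomes: "The occurrence of adverse events between the groups is compared using a chi-squared test or Fisher’s exact test". Events are graded with the Common Toxicity Criteria and also described.

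The capture rule is in Adverse event reporting and harms {22}: "All AEs reported spontaneously by the subject or observed by the research physician, or his staff will be recorded". The same section defines an AE broadly, as any undesirable experience during the study, related or not.

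The contact schedule differs by arm. Explanation for the choice of comparators {6b} says, for T2S: "Two weeks after ULT cessation an extra blood sample is obtained to check for any changes in blood counts and kidney and liver function", and "A telephone consult is planned three weeks after ULT cessation to verify that ULT has indeed been stopped". Participant timeline {13} confirms that this applies to T2S patients, for whom "a telephone consult is scheduled one week later to discuss results". The contacts described for both arms are clinic visits at baseline, month 12 and month 24, a monthly flare questionnaire and a three-monthly questionnaire set.

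**The concern.** A between-arm comparison of AE occurrence is fair only if an event has the same chance of being found in each arm. Here one arm has a planned laboratory screen and a planned conversation with staff early in follow-up. The other has neither, and its next planned visit after baseline is month 12. A raised liver enzyme, a lower eGFR or a minor complaint mentioned on the call can be recorded in T2S. The same finding in T2T has no scheduled occasion to be seen, and may have resolved by month 12.

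T2S is the arm the trial expects to do worse, so the bias runs with the hypothesis. It also falls early after cessation, a period that the secondary objectives single out for cardiovascular events. The article discusses expectation bias for flares and for restarting ULT (Who will be blinded {17a}; Discussion) but not unequal detection of AEs. Nothing in it keeps findings from the T2S-only contact out of the test. At stake is a secondary safety comparison; the primary outcome is untouched.

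**Working it through.** **1. Scheduled contacts, side by side (from the text).**

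| | T2T | T2S |
|---|---|---|
| Clinic visits | baseline, months 12 and 24 | baseline, months 12 and 24 |
| Questionnaires | monthly and three-monthly | monthly and three-monthly |
| Safety sample after stopping | none described | one, 2 weeks after cessation |
| Call to discuss results | none described | one, a week after the sample |

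Table 2 has ULT stopped between baseline and week 6, so the extra sample falls at 0 + 2 = 2 to 6 + 2 = 8 weeks from baseline. The schedule in Figure 3 should be checked for any T2T counterpart; the text mentions none. The optional T2S sub-study at one site, with three-monthly research samples, is a further T2S-only contact in a subset and is not counted here. Section {18b} places a call 2 weeks after cessation, whereas {6b} and {13} place it at 3 weeks. These passages must be reconciled, but the point does not depend on which applies.

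**2. The plan's own figure.** The AE comparison has no stated rate, power or sample size. The only number to borrow is the 278 analysable patients for the primary outcome, 139 per arm. The unpooled one-sided formula reproduces it: (1.645 + 0.842)² × (0.04 × 0.96 + 0.12 × 0.88) / 0.08² = 139.1 per arm. The pooled version gives 142 per arm (284).

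**3. Size of the bias under stated assumptions.** Let p be the true proportion with any AE, equal in both arms. Let q be the share of otherwise AE-free T2S patients in whom the extra contact yields a recorded AE. Neither is in the documents.

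- Recorded proportion: T2T = p; T2S = p + (1 − p)q.
- Spurious excess: (1 − p)q.
- Chance that a two-sided 0.05 two-proportion test shows a significant T2S excess: Φ{[(1 − p)q − 1.96·SE₀]/SE₁}, where SE₀ is the pooled and SE₁ the unpooled standard error at 139 per arm. With no bias this is 0.025.

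Example, p = 0.40 and q = 0.10: excess = 0.60 × 0.10 = 0.06; SE₀ = √(2 × 0.43 × 0.57/139) = 0.0594; SE₁ = √((0.40 × 0.60 + 0.46 × 0.54)/139) = 0.0593; (0.06 − 0.1164)/0.0593 = −0.95, giving 0.171.

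| p | q = 0.02 | q = 0.05 | q = 0.10 | q = 0.20 |
|---|---|---|---|---|
| 0.20 | 1.6 points; 0.051 | 4.0; 0.124 | 8.0; 0.345 | 16.0; 0.848 |
| 0.40 | 1.2; 0.040 | 3.0; 0.073 | 6.0; 0.171 | 12.0; 0.519 |
| 0.60 | 0.8; 0.034 | 2.0; 0.053 | 4.0; 0.101 | 8.0; 0.283 |

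With 155 per arm (310/2, all enrolled) the pattern is the same: p = 0.40 and q = 0.10 gives 0.185. I carry forward q = 0.02 to 0.10. A yield of one in five from a single sample and call is shown as an extreme.

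**4. Which events are exposed.** Blood count, kidney and liver abnormalities are exposed directly, and minor complaints through the call. Deaths, strokes, infarctions and hospitalisations would normally come to light without one early call. Arrhythmia, which the cardiovascular definition includes without requiring admission, is the one component that a call might surface.

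**The case against.** The strongest reply is that one sample and one call in 24 months is little, and that its yield is unknown. At p = 0.60 and q = 0.02 the excess is 0.8 points and the false-signal probability 0.034 against 0.025, which is negligible. That stands. A reader might infer that T2S will show more events from detection alone. The documents do not support this: no yield is given, and a true difference in either direction could outweigh the bias.

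A reader might also infer that every abnormal value at the extra sample becomes an AE, or that all other events depend on patients volunteering them. Neither follows. The article does not say when a laboratory value counts as an AE, and the full protocol may. The capture rule also covers events that staff observe, and both arms share three visits and the questionnaires. Systematic AE questioning at those visits may be described in the full protocol, but it would not give T2T an early laboratory test.

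The article does not state that all AEs go into a single any-AE test, so the table above is one reading of an occurrence comparison. Renal function is described as a change, a measured quantity comparable only where both arms have values, so naming the common time points makes explicit what is largely implied.

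Finally, contacts prompted by flares or by restarting ULT are part of the strategy under test in a pragmatic trial. They are not a schedule artefact and are not part of this point.

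**Conclusion.** The point holds as a detection bias of known direction and unknown size. Followed as written, the plan compares AE occurrence between an arm with a scheduled early safety screen and an arm without one, and has no rule for findings that only the screen could produce. With an assumed AE proportion of 20 to 60% and an assumed yield of 2 to 10%, the spurious excess is 0.8 to 8.0 percentage points. The chance of a significant T2S excess with no true harm is then 0.034 to 0.345, against 0.025 without bias. All of this rests on those assumed rates, on 139 per arm and on an any-AE comparison.

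The concern is confined to laboratory, minor and early non-serious events. It does not show that the comparison of serious cardiovascular events is unsound, and it does not touch the primary outcome. It is worth correcting because the bias is avoidable at almost no cost, and because an early T2S excess could not otherwise be told apart from extra testing.

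**What to change.** Add three rules to the AE analysis under Statistical methods {20a}, before results are seen:

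1. Base the between-arm comparison of laboratory and renal findings on the time points common to both arms: baseline, month 12 and month 24.
2. Flag AEs first detected at the T2S-only sample or call, and list them separately.
3. Report the between-arm AE comparison twice, with and without the flagged events. Leaving them out may over-correct, since some would have surfaced later anyway, so the two results should be read together.

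Keep the extra T2S safety check and the existing AE capture in both arms. The medical consumption questionnaire (iMCQ) should not replace AE capture: it records healthcare use and would lose events that led to none.

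The cost is a source flag on each AE (or a match of its date to the T2S contact) and one additional table. No new visits or data are needed. The drawback is that the restricted comparison could leave out a true early laboratory effect of stopping ULT; the separate listing and the unrestricted analysis would still show it.
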